### Statistical Analyses

The demographic characteristics of all participants will be summarized using descriptive statistics, such as means (SDs), frequencies, and ranges, which will be presented in a tabular form. Statistical analysis of the data will be performed using the SPSS statistical software (version 2, SPSS Inc). *P*<.05 will be considered statistically significant. The normality of the data will be assessed using the Kolmogorov-Smirnov test. Numerical variables will be presented as mean (SD) or median (IQR) values, while categorical variables will be presented as frequency (percentages). To determine differences in numerical variables between the therapeutic cookies and placebo groups, independent sample *t* tests or Mann-Whitney *U* tests will be used. The same tests will also be used to compare alterations in outcome variables between the 2 groups. For within-group comparisons, paired-sample *t* tests or the nonparametric Wilcoxon test will be used. To account for the effects of confounding factors, a general linear model will be applied. In addition, analysis of covariance will be used to account for the effects of confounding factors when appropriate.

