### Sample Size Calculation

With a significance level (type 1 error) of 5% and a statistical power of 90%, the sample size for each study group will be calculated to be 25, using a 2-sided *t* test, taking into account the changes in MMP-9 values as one of the primary outcomes [20]. We will clarify that the block lengths in our randomization process will be constant. To account for an estimated attrition rate of approximately 20% during the study, the final sample size will be increased to 30 participants in each group. The estimation of the sample size is calculated using the following formula:

In this formula, α=5%, 1-β=90%, SD1=2.7, SD2=2.7, *d*=2.5.

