### Blood Sample Collection

Blood samples for the identification of MMP-9 will be collected from each participant at a specific time point in the morning, following an overnight fast. The samples will be drawn at approximately 8 AM to ensure consistency and minimize potential variations in MMP-9 levels due to diurnal rhythms. This fasting state collection will aim to provide a baseline measurement of MMP-9 levels. Additionally, blood samples will be collected both before and after the intervention involving the administration of cookies to assess potential changes in MMP-9 levels in response to the intervention.

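### MMP-9 is to be compared by unadjusted change scores; an ANCOVA on the baseline MMP-9 already collected would be more precise and should be named as the primary analysis

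*Protocol article*

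**What the plan says.** Four places in the protocol article bear on this.

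- **Statistical Analyses, between-group tests.** "The normality of the data will be assessed using the Kolmogorov-Smirnov test". Groups are compared by independent t test or Mann-Whitney test, and "The same tests will also be used to compare alterations in outcome variables between the 2 groups".
- **Statistical Analyses, adjustment.** A general linear model for confounding factors is planned without condition. In addition, "analysis of covariance will be used to account for the effects of confounding factors when appropriate". No covariate is named for either, baseline MMP-9 is not mentioned as one, and no analysis is called primary.
- **Sample Size Calculation.** The trial is sized on a two-sided t test, "taking into account the changes in MMP-9 values as one of the primary outcomes", with "SD1=2.7, SD2=2.7, *d*=2.5". The result is stated as follows: "the sample size for each study group will be calculated to be 25". This is raised to 30 per arm for about 20% attrition.
- **Blood Sample Collection.** For MMP-9, "blood samples will be collected both before and after the intervention", so a baseline value will exist for each randomised participant who is sampled.

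**The concern.** When an outcome is measured before and after treatment in a randomised trial, subtracting the baseline fixes its coefficient at 1. With equal variances the best coefficient is the pre-post correlation, which is below 1 whenever there is measurement error or within-person variation. A change score therefore adjusts too much for baseline and carries avoidable noise. ANCOVA estimates the coefficient from the data.

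What is at stake is precision in a small trial. Thirty per arm less 20% leaves 24 completers, slightly fewer than the 25 that the calculation calls for, so the planned test has little power to spare. The information that would make up the difference is already collected, but the plan does not commit to using it. Adjustment is described only as a remedy for unnamed confounding, whereas in a randomised comparison its main use is to reduce residual variance.

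**Working it through.** **Inputs.** From Sample Size Calculation: two-sided alpha 0.05, power 0.90, SD 2.7 in each arm, difference 2.5, 25 per arm, 30 after attrition of about 20%. Because that section speaks of changes, 2.7 is read as the SD of change; the other reading is checked below. The pre-post correlation rho is not in the article. It is assumed to be 0.3 to 0.7, with higher values shown as well. Equal pre and post variances are also assumed.

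**1. The plan's own figure.** n per arm = 2(1.960 + 1.282)² × 2.7² / 2.5² = 24.51, rounded up to 25. The stated figure reproduces. (The exact noncentral t gives 89.4% power at 25 and needs 26 for 90%, a trivial difference.)

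**2. Power of the planned test at the expected number of completers.** 30 × (1 − 0.20) = 24 per arm. The noncentrality is 2.5 / (2.7 × √(2/24)) = 3.21 on 46 df, which gives power of 88.1%.

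**3. Variance ratio.** With s the SD of one measurement, Var(change) = 2s²(1 − rho) and Var(ANCOVA) = s²(1 − rho²). The ratio is (1 + rho)/2, so the ANCOVA residual SD is 2.7 × √((1 + rho)/2).

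**4. Cost of the covariate.** Estimating one slope inflates the variance by 1 + 1/(2n − 4) = 1 + 1/44 = 1.023 at n = 24, and the test loses one degree of freedom.

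**5. Results at 24 per arm.**

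| rho (assumed) | Variance ratio | Ratio net of covariate cost | Residual SD | ANCOVA power | Change-score power |
|---|---|---|---|---|---|
| 0.3 | 0.65 | 0.67 | 2.18 | 97.1% | 88.1% |
| 0.5 | 0.75 | 0.77 | 2.34 | 94.8% | 88.1% |
| 0.7 | 0.85 | 0.87 | 2.49 | 92.0% | 88.1% |
| 0.8 | 0.90 | 0.92 | 2.56 | 90.5% | 88.1% |
| 0.9 | 0.95 | 0.97 | 2.63 | 89.0% | 88.1% |
| 0.95 | 0.975 | 0.997 | 2.67 | 88.2% | 88.1% |
| 1 | 1.00 | 1.02 | 2.70 | 87.4% | 88.1% |

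Residual SDs are before the covariate cost; the powers include it.

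**6. If 2.7 is the SD of a single measurement.** By the normal approximation of step 1, the change score needs 35, 25 and 15 per arm at rho 0.3, 0.5 and 0.7, and ANCOVA needs 23, 19 and 13. The direction does not depend on the reading.

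**7. Does the normality check damage the error rate?** In a simulation with 25 per arm and 4,000 runs per setting, a mechanical rule that let a Kolmogorov-Smirnov test (Lilliefors form) choose between t and Mann-Whitney kept its size at about 5%, for normal and for lognormal data.

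**8. Scale.** In the lognormal runs (an assumed shape), with a treatment effect present, power was 0.84 to 0.87 for the t test of change, 0.90 to 0.95 for raw-scale ANCOVA and about 0.96 for Mann-Whitney. If MMP-9 is skewed, ANCOVA on the raw scale is not the best choice, so the scale has to be fixed together with the model.

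**The case against.** The strongest reply is that nothing in the plan is invalid. The change-score test is unbiased over randomisation and matches the test on which the trial was sized. A general linear model is planned without condition, so some adjustment is intended, and covariate lists are commonly left to a fuller document that is not shown. All of this stands, and it limits the point to efficiency. It does not remove it: the article states which comparison it will make, and neither adjusted model is tied to baseline MMP-9.

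The figures have limits too. The gain depends on a correlation that the article does not give and is negligible at 0.9 or more. The powers are on the raw scale and do not measure the gain on a log scale.

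Three stronger readings are tempting, and the article supports none of them.

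- **Inflated type I error.** Taking the smallest P among t, Mann-Whitney and ANCOVA gave a type I error of 7 to 9% in the same simulation. The text does not rule that out but nowhere plans it. Nor are there four separate candidate tests: t and Mann-Whitney are alternatives, and ANCOVA is itself a general linear model. Even the switch on the normality result is implied by the order of the sentences and not stated.
- **A biased estimate.** A chance baseline gap of 0.5 SD shifts the change-score estimate by 0.5(1 − rho), or 0.35, 0.25 and 0.15 SD at rho 0.3, 0.5 and 0.7. That holds conditionally on an observed imbalance; it is not a bias of the design.
- **Baseline significance tests, or efficacy claims from within-group tests.** Demographics are to be summarised descriptively, and nothing says that the paired tests will support efficacy.

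**Conclusion.** The point holds as a recommendation on efficiency that the sponsor should adopt, not as a correction of an invalid test. At 24 completers per arm, baseline ANCOVA raises power from 88.1% to between 92.0% and 97.1% for rho of 0.7 down to 0.3. It keeps power above the planned 90% up to rho of about 0.8. The gain falls to about one point at 0.9 and vanishes near 0.95; at rho 1 ANCOVA would lose less than one point. These sizes rest on SD 2.7 being that of the change, on equal pre and post variances, on an assumed rho, and on approximate normality on the analysis scale.

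**What to change.** In Statistical Analyses, name one primary analysis: ANCOVA of post-intervention MMP-9 on randomised group and baseline MMP-9. State the scale in advance, for example log for both outcome and baseline, and do not let a normality test choose it. Keep the t or Mann-Whitney test of change as a sensitivity analysis. List any further covariates before the data are seen. Use the same model for ABI and random blood glucose, each with its own baseline, which the participant timeline already schedules.

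The cost is a few sentences, one degree of freedom (about 2% of variance at 24 per arm) and no new measurements. If the log scale is chosen, the effect becomes a ratio of geometric means in place of a mean difference, and the planning values of 2.5 and 2.7 no longer apply directly to the primary model.

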### Ethical Considerations

Prior to the commencement of this study, ethical review and approval were obtained from the local ethical committee of the Public Health Faculty of Universitas Hasanuddin, Makassar, Indonesia (approval number 10973/UN4.14.1/TP.01.02/2023). This study adheres to all applicable ethical guidelines and regulations governing research involving human subjects.

Informed consent was obtained orally from all participants involved in the primary and data collection. In the case of secondary analyses of research data, the original informed consent, as approved by the institutional review board, explicitly allowed for secondary analyses without the need for additional consent. Participants were informed that their data would be used for research purposes beyond the initial study.

The privacy and confidentiality of participants in this research were rigorously protected. All data collected were anonymized or deidentified to ensure the confidentiality of participants. Any personal identifying information was removed, and data were stored securely to prevent unauthorized access.

Participants received compensation in the form of monetary compensation for their time and participation. The compensation amount was set at IDR 100,000/week (US $7-8/week) and was disclosed to participants during the informed consent process.

The study has been registered on the Thai Clinical Trials Registry website (TCTR20230502001). Any changes to the study protocol will be communicated to the Trials journal.

## Results

The recruitment and testing phase started in January 2024. The study is scheduled to be completed by the end of March 2024. Data analysis will commence in April 2024, and the publication of the results is anticipated in the same year (2024).

## Discussion

### Expected Outcomes

This study focuses on the significant issue of DFUs in patients with diabetes and the importance of preventing DFUs and associated amputations. DFUs affect approximately 6.4% of the global diabetic population [29], reduce quality of life, prolong hospital stays, and lead to a considerable number of lower limb amputations globally each year [30]. Notably, peripheral neuropathy, the most prevalent type of diabetic neuropathy, plays a critical role in the development of DFUs due to its impact on sensory function and increased susceptibility to ulcers [31].

In the realm of diabetic neuropathy, MMP-9 is considered crucial in its progression and holds a potential target for treatment purposes [32]. Furthermore, it is important to acknowledge that elevated blood sugar levels and insulin resistance in diabetes contribute to the generation of ROS, intensifying the complications associated with the disease [33]. The activity of MMP-9 is heightened in individuals with diabetes, partially due to increased production by vascular endothelial cells and the influence of ROS [33].

MMP-9 plays a role in increasing tissue inflammation, which is one of the contributing factors to diabetic neuropathy [32]. By reducing MMP-9 activity, we can decrease inflammation that harms peripheral nerves. MMP-9 can damage blood vessel walls, leading to impaired blood circulation to nerves [34]. Reducing vascular damage can enhance blood flow to nerves, aiding in the prevention of neuropathy. Additionally, MMP-9 can harm the extracellular matrix surrounding nerve cells. If MMP-9 is reduced, the extracellular matrix may be better preserved, offering improved protection against nerve damage. Excessive MMP-9 activity has been linked to apoptosis or nerve cell death [35]. By reducing MMP-9 activity, we can help safeguard nerve cells from death, which contributes to neuropathy. Furthermore, MMP-9 can contribute to nerve degeneration and loss of nerve function. Lowering MMP-9 can assist in slowing down or halting this degenerative process [36].

The main interest of this study is the concept of diabetic-friendly cookies, which can stimulate insulin production in the body by boosting the beta pancreas and decreasing the glycemic index through the mechanism of MMP-9 reduction. To further support the reduction in glycemic index and prevent DFU, the suitable herbal ingredients for combination in these cookies are Golden Rice and *P. crocatum*. They are known for their safety and therapeutic activities, such as anti-inflammatory effects, wound healing activities, antibacterial properties, antioxidant effects, and antihyperglycemic effects. The oral consumption of *P. crocatum* and Golden Rice extracts has been proven to be safe in humans. A functional beverage containing *P. crocatum* was developed, demonstrating significant antioxidant and antidiabetic properties, and it was acceptable by consumers [37]. A recent study has also identified the use of *P. crocatum* as a healthy food and drink option for reducing blood sugar levels in patients with diabetes mellitus [38].

The reduction of MMP-9 as the study objective may not be sufficient to completely prevent diabetic neuropathy, as this disease is highly complex and involves numerous factors. However, reducing MMP-9 can be a potentially helpful step in mitigating the risk and impact of diabetic neuropathy, particularly when combined with other appropriate treatment approaches.

This study explores the biological mechanisms underlying diabetic neuropathy and the potential role of MMP-9, providing valuable insights into the pathophysiology of DFUs and potential therapeutic targets. The safety and acceptance of *P. crocatum* and Golden Rice extracts in humans, as demonstrated in previous studies, support the feasibility of incorporating these ingredients into dietary interventions to prevent DFUs.

Although this study delves into biological mechanisms and potential therapeutic interventions, the translation of these laboratory findings into clinical applications may require further research and clinical trials. The study may have limitations regarding the generalizability of its findings. It is essential to acknowledge that dietary interventions may have varying effects on individuals with different demographics, comorbidities, and genetic factors. The study duration is also considered a limitation, as it does not cover a long-term assessment of the effects of cookies and herbal ingredients.

### Conclusions

In conclusion, the findings of this study hold the potential to significantly influence the strategies used by health care practitioners in enhancing diabetes self-management, particularly in the domain of therapeutic snacking, for patients diagnosed with diabetes mellitus. Considering the substantial burden of DFUs on patients, health care systems, and society, it is crucial to focus on preventing DFUs and amputations. Exploring potential therapeutic targets like MMP-9 and using natural ingredients like *P. crocatum* in combination with other diabetes-friendly products may provide promising avenues for preventing DFUs and improving the outcomes for patients with diabetes. Further research and clinical trials would be necessary to validate the efficacy and safety of such interventions. These insights can inform the selection of strategies for health care practitioners to enhance diabetes self-management, thereby benefiting patients with diabetes mellitus. 

## Appendix

Multimedia Appendix 1 SPIRIT Checklist.

Multimedia Appendix 2 Consort checklist.

## Abbreviations

ABI: ankle-brachial index
DFU: diabetic foot ulcer
MMP-9: matrix metalloproteinase-9
*Piper crocatum*: *P. crocatum*
ROS: reactive oxygen species
SPIRIT: Standard Protocol Items: Recommendations for Interventional Trials
